| 4.Subject of the study and its aims  (Hypothesis divided into primary and secondary hypotheses) | Primary Hypothesis:  Compared to conventional therapy an intra-operative goal-directed haemodynamic management by monitoring with LiDCOrapid or oesophageal Doppler improves haemodynamics measured by stroke volume (SV) in patients undergoing elective liver resection.  Secondary hypothesis 1:  Compared to conventional therapy an intra-operative goal-directed haemodynamic management by monitoring with LiDCOrapid or oesophageal Doppler reduces the incidence of perioperative dysfunction (cerebral, pulmonary, renal, abdominal and cardiovascular), the amount of intraoperative blood loss and the postoperative incidence of infections and quality of life in patients undergoing elective liver resection.  Secondary hypothesis 2:  Compared to conventional therapy an intra-operative goal-directed haemodynamic management by monitoring with LiDCOrapid or oesophageal Doppler the postoperative liver function in patients undergoing elective liver resection.  Study groups:  The administration of the volume and catecholamine therapy is carried out by:  1.) Conventional standard therapy  2.) Goal-directed haemodynamic management by monitoring with oesophageal Doppler  3.) Goal-directed haemodynamic management by monitoring with LiDCOrapid  Primary outcome measure:  Stroke volume before intra-operative start of liver resection  Secondary outcome measures:   - Intra-operative and post-operative haemodynamic parameters - Intra-operative and post-operative blood loss - frequency of organ dysfunctions (cerebral, pulmonal, renal, abdominal, cardiovascular) - Post-operative liver function (LiMAx-test, ICG-Clearance, liver Doppler, laboratory tests: enzymatic and chemical parameters) - Peri-operative weight change - Post-operative incidence of infections - Satisfaction of the patients, the surgeons and anaesthetists - Time to fulfilling discharge criteria - Length of intensive care stay and hospital stay (LOS) - Quality of life measure (EQ-5D) - Laboratory tests: peri-operative endothelial and immunological alterations |
| 5. Purpose of the study | The haemodynamic management of patients undergoing liver resections by anaesthesiology is determined by the goal to minimize the intraoperative bleeding during the surgical incision of the liver . This goal is reached by a hypovolaemic volume and fluid strategy to reach a low central-venous pressure. Thereby the backwards flow of the blood from the right heart by the liver veins to the resection surface of the liver is minimized and the blood loss will be reduced. This management is constituted by studies of the 1990ies as a possibility to reduce perioperative morbidity and mortality .  In recent years the surgical patient population changed due to a higher number of comorbidities especially of cardiovascular diseases. According to our clinical experiences this implies that some patients show a substantial drop of stroke volume and cardiac output with consecutive decreased perfusion especially of the splanchnic area induced by this restrictive fluid and volume therapy.  With the oesophageal Doppler and the LiDCOrapid there are two minimal-invasive monitors to offer valid measurements of stroke volume and therefore offer the possibility to guide volume and catecholamine therapy. In colorectal and gynaecological-urological resections and in traumatology the benefit of advanced monitoring on hospital length of stay is well documented in the literature (table of studies in appendix 1). But these studies direct on an intraoperative optimization of cardiac preload according to the Frank-Starling mechanism. For liver resections this approach is not feasible due to the increased risk of intraoperative bleeding. Therefore we created an algorithm for a restrictive volume management by maintaining cardiac output and splanchnic perfusion without preload optimization during the course of surgery. According to our knowledge up to date there is no algorithm in the literature for a goal-directed, restrictive volume management during liver surgery.  The goal of this study is to compare the developed intraoperative, restrictive, goal-directed volume protocol based on advanced haemodynamic monitoring versus standard of care to evaluate the impact on stroke volume as primary outcome measure and to further evaluate the impact on the influence on surgical proceedings and postoperative parameters as secondary outcome measures.  A further goal of this study is with the collaborations of the colleagues of the clinic of general, visceral and transplantation surgery to describe the particular perioperative modules and by their standardization to increase the quality and transparency of the study results. |
| 6. Which of the following regulations apply -   1. Medicinal product law -in accordance with § 20 MPG (equipment does not possess a certificate of conformity or does possess such a certificate but another indication is examined or it will be more invasive or other demanding investigations will be performed) or   - in accordance with § 23MPG?   1. Radiation protection regulation § 23 2. X-ray regulation § 28 a 3. Genetic engineering law 4. Data protection acts | Data privacy act |
| 7. If necessary: Designation and chacharacteristics of Test Products (e.g. devices with MPG studies, please attach information as an appendix) | Not applicable |
| 8. Main results of prior clinical tests or reasons for not performing such tests | The methods of minimal-invasive monitoring of the circulatory parameters are sufficiently evaluated for their use in human beings. The studies are listed in appendix 1 and 2 and are further mentioned in section 9. Due to these explanations we set aside displaying preclinical studies. |
| 9. Main content and results of previous studies/applications of the products to be examined in this study | The oesophageal Doppler is tested in clinical studies since approximately 15 years. A selection of studies is outlined in appendix 1. The oesophageal Doppler in combination with a volume protocol based on his values could show a benefit in cardiovascular, urological-gynaecological, abdominal and traumatological surgery.  Conducted comparisons with other haemodynamic monitoring devices to determine cardiac output showed a good correlation of the measured values between the methods.  The method of advanced haemodynamic monitoring by the LiDCOrapid was tested against validated methods in intensive care medicine as well as for intraoperative use (studies appendix 2). It showed a good correlation during different haemodynamic situations against established methods. But in contrast to the oesophageal Doppler there are no studies examining the influence of a LiDCOrapid driven algorithm on hospital length of stay.  The measurements of liver function should be performed by the established ICG-Clearance as well as by the newly developed LIMAX-Test. This technique is based on the kinetic analysis of an administered intravenous bolus of 13C-Methacetin (2ml/kg KG).  The chemical master reaction is the demethylation by the CYP1A2 in the liver. The formed 13CO2 will be eliminated by respiration and measured online by a non-dispersive infrared analyzer directly on the bedside and therefore offers a direct value of the metabolic capacity of the liver . Both methods are established methods of the Department of general, visceral and transplantation surgery of the Charité – Universitaetsmedizin Berlin, Campus Virchow Clinic for the pre- and postoperative evaluation of patients undergoing liver resection surgery and are correlated during the clinical course to the sonography of the liver vessels and MRI exams of the liver. |

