| 12. Risk control measures | The dangers of placing the oesophageal probe comprise oesophageal injury and nasopharyngeal bleeding. For this reason pre-existing pathology or recent operations in the area of the oesophagus or nasopharyngeal cavity represent risk factors for these complications and should be regarded as contraindications to study participation.  The siting of the oesophageal probe takes place under the strict supervision of an anaesthetist and all patients will be monitored post-operatively until their discharge or for 30 days. |
| 13. Study termination criteria | Under the following conditions premature separating of a patient from the study occurs in accordance with the abort criteria:  The following events can be regarded as reasons for termination:  • personal wish of the patient  • every other situation, where in the opinion of the study physician, further participation in the trial would not be in the best interests of the patient  • unblinding in the case of a medical emergency  • significant protocol breaches  • Subsequent occurrence of an exclusion criterion  A premature cessation of the study and/or an abandonment of the entire study can occur in the following circumstances:  • Decision of the study leader where untenable risks exist according to risk-benefit analysis  • new (scientific) developments during the course of the study demonstrating a risk to participants by further continuation of the study (a positive risk-benefit ratio is no longer applicable) |
| 14. Number, age and sex of participants | There are no studies in the literature for the primary and secondary endpoint that show reliable data to enable a statistical calculation of the number of patients that would be needed.  Therefore this study is planed as a pilot study including 20 patients per group that means overall 60 patients are included. In this study no gender-based selection of the study patients will be performed. Man and woman aging more than 18 years are included in the study. |

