| 15. Description of statistical methods and biometric basis for required number of cases with signature of statistician | For all endpoints of the study explorative data analyses will be performed and descriptively analysed. Because of the small sample sizes and possible outliers and/or skew distributions, the primary and secondary endpoints will be analysed using non-parametric statistical tests (qualitative data: Fisher’s exact test, quantitative data: Mann-Whitney-U test for independent groups or Wilcoxon-test for paired observations).  All test will be performed with an alpha error = 5% (two-sided). The calculated p values will be considered as explorative and do not allow confirmative generalization. Due to the same reason we do not perform alpha adjustment for multiple testing.  As we can not perform a calculation of the sample size the number of patients to be included in this study follows objective considerations and the clinical possibilities to perform the conductance of this pilot study. With the results of this study a consecutive prospective randomized study with calculation of the sample size shall be initiated.  The analysis of the study results will be performed according to the “intention-to-treat” as well as to the “per-protocol” principle.  The numerical calculations are performed with the statistical program SPSS, Version 17, Copyright SPSS, Inc., Chicago, Illinois 60606, USA. |

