| 16.  a. Statement of exclusion criteria, with explanation if necessary | **Inclusion criteria:**   - Written informed consent from patient - Patients undergoing elective liver resection in Charité - University Medicine Berlin, Campus Virchow-Clinic   **Exclusion criteria:**   - Aged less than 18 years - No written informed consent from patient - For female patients: pregnancy or lactation - Inability to communicate freely in the German language - Lack of willingness to safe and hand out pseudonymised data within the clinical study - Simultaneous participation of the patient in another study - Accommodation in an institution due to an official or judicial order - Members of staff of the Charité - Unclear history of alcohol used disorder - Advanced disease of the oesophagus of nasopharyngeal cavity - Operations in the area of the oesophagus or nasopharynx within the last two months - History of bleeding tendency e.g. Von Willebrands disease - Neurological or psychiatric disease - Chronic heart failure New York Heart Association (NYHA) class IV - American Society of Anaesthesiologists (ASA) classification greater than IV - Chronic renal failure with dependency of haemodialysis - Existence of a pulmonary oedema in the pre-operative chest x-ray - History of intracranial haemorrhage within one year - Allergy to gelatin |
| 16.  b. **Participant information** *(who gives this statement verbally and indicates how much time remains between declaration and consent, otherwise by reference to their contents in an appendix* | see appendix |
| c. **Declaration of consent** *(reference to their contents in an appendix is possible)* | see appendix |
| d. If necessary **obtain information and consent from legal representatives** *( also if required describe the procedure to obtain a judicial review)* | Not applicable |
| 17. Methods to recruit study participants (notices, newspaper advertisements, etc) | All patients undergoing abdominal surgery in the Charite Campus Virchow will be screened to see if they fulfil the inclusion criteria. |
| 18. If necessary: **Reason for inclusion and justification of therapeutic use in individuals who are under-age and/or are incapable of giving consent** | Not applicable. |

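### Post-operative LiMAx and ICG clearance are to be compared between arms without using the pre-operative value or the extent of resection, an avoidable loss of precision for secondary hypothesis 2

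*Protocol*

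**What the plan says.** Secondary hypothesis 2 (item 4) concerns post-operative liver function, and the matching outcome is "Post-operative liver function (LiMAx-test, ICG-Clearance, liver Doppler, laboratory tests: enzymatic and chemical parameters". It is listed as a post-operative quantity; item 4 mentions neither a change score nor a reference value.

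The inclusion criterion in item 16a is "Patients undergoing elective liver resection in Charité - University Medicine Berlin, Campus Virchow-Clinic". None of the exclusions concerns the extent of resection, the remnant or underlying liver function.

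Item 15 assigns the tests for primary and secondary endpoints together: "quantitative data: Mann-Whitney-U test for independent groups or Wilcoxon-test for paired observations". It names no covariate or stratification factor. It also says "All test will be performed with an alpha error = 5% (two-sided" and "The calculated p values will be considered as explorative and do not allow confirmative generalization", and that a later randomised study with a sample-size calculation is to be built on the results.

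Item 14 sets the size of this pilot: "including 20 patients per group that means overall 60 patients are included". Item 9 presents LiMAx and ICG clearance as established methods of the surgical department "for the pre- and postoperative evaluation of patients undergoing liver resection surgery".

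**The concern.** If LiMAx measures metabolic capacity, as item 9 says, the value after resection depends on the capacity before surgery and on the share taken out. Neither is an effect of the haemodynamic management. With no limit on extent, both can vary widely between patients, and an unadjusted rank test treats all of that variation as noise.

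Two things are at stake. With 20 patients per arm, the comparison for secondary hypothesis 2 is less sensitive than the available data allow. And if the follow-on trial is sized on the spread of unadjusted values, that spread includes variance that a covariate could have removed, so the trial comes out larger than it needs to be.

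**Working it through.** **Inputs from the protocol.** 20 per arm in three arms (3 × 20 = 60, which agrees with item 14); two-sided alpha 5% (item 15); Mann-Whitney U as the between-group test (item 15). The protocol gives no SD, effect size, power or mix of resections, so there is no figure of its own to reproduce beyond the 60.

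**Assumption.** R² is the share of the variance of the post-operative value explained by the pre-operative value and the extent together. The documents do not give it; the range taken is 0.25 to 0.75. Effects are in units of the total SD.

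**Step 1: detectable difference, 20 v 20, 80% power.**
- Normal approximation: (1.960 + 0.842) × √(2/20) = 0.886 SD.
- Mann-Whitney, relative efficiency 3/π: 0.886 / √(3/π) = 0.907, about 0.91 SD.
- Adjusted, normal approximation: 0.886 × √(1 − R²).

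| R² | Adjusted | Adjusted, with the 3/π factor kept |
|---|---|---|
| 0.25 | 0.77 SD | 0.907 × √0.75 = 0.79 SD |
| 0.50 | 0.63 SD | 0.907 × √0.50 = 0.64 SD |
| 0.75 | 0.44 SD | 0.907 × √0.25 = 0.45 SD |

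The last column is the like-for-like comparison with 0.91 for a rank-based adjusted analysis; the difference is minor.

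**Step 2: simulation** (3,000 runs per setting, normal data, half the resections major, raw Mann-Whitney against ANCOVA).

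| | R² = 0.25 | R² = 0.50 | R² = 0.75 |
|---|---|---|---|
| Raw, no effect | 5.0% | 5.3% | 5.4% |
| Raw, 0.5 SD | 32% | 32% | 30% |
| Adjusted, 0.5 SD | 39% | 56% | 85% |
| Raw, 0.8 SD | 66% | 65% | 66% |
| Adjusted, 0.8 SD | 79% | 93% | >99% |

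The error rate of the unadjusted test under random allocation is about 5%. What is lost is power.

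**Step 3: consequence for a follow-on trial.** N per arm for 80% power at 0.5 SD is 2 × (2.802)² × (1 − R²) / (0.5² × 3/π). Unadjusted, this gives 66. Adjusted, it gives 50, 33 and 17 at R² of 0.25, 0.50 and 0.75. The variance ratio, unadjusted to adjusted, is 1/(1 − R²), from 1.3 to 4.

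**Step 4: is an R² in that range reasonable for LiMAx?** An illustrative model, all inputs assumed: post = pre × (1 − resected fraction) × noise; fraction uniform on 10–60%; pre-operative CV 20–30%; residual CV 15–25%. On the log scale, extent contributes variance 0.053. Baseline and extent then explain from (0.053 + 0.040)/0.1555 = 60% to (0.053 + 0.090)/0.1655 = 86%. If the fraction runs only from 10 to 40% (variance 0.014), the range is 46–82%.

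On the 10–60% model, the 95% CI factor for the between-arm ratio, exp(1.96 × √(2 × var/20)), is:
- unadjusted (var 0.1155 to 0.2055): 1.23–1.32;
- ratio to own baseline only (0.0755 to 0.1155): 1.19–1.23;
- baseline plus a perfect minor/major split at 35%, which captures about 73% of the extent variance (0.0368 to 0.0768): 1.13–1.19;
- baseline plus the exact resected fraction (0.0225 to 0.0625): 1.10–1.17.

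The last line is a ceiling, because the exact fraction is not known before surgery.

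**Step 5: chance imbalance.** Two arms of 20 differ by 4 or more major resections with probability 0.27 if half of resections are major, and 0.23 if 30% are. On the model of Step 4, mean log(1 − fraction) differs by 0.395 between minor and major, so a difference of 4 in 20 shifts the ratio by exp(0.2 × 0.395) = 1.08. That is well inside the unadjusted CI factor.

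**The case against.** The best case for the plan is this. It is a declared pilot, hypothesis 2 is secondary, and the p values are exploratory. The primary outcome is stroke volume before resection starts, so the amount of liver removed cannot disturb it. Item 15 names families of tests, not the quantity that enters them; a Mann-Whitney test on the change from baseline would be compatible with its wording. Covariates, derived variables and days for a secondary endpoint are often left to a statistical analysis plan, and if baseline values are routine an adjusted analysis can still be added.

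Much of this stands, and it limits the weight of the point. It does not remove it. Item 4 lists the post-operative quantity, and item 15 names an unadjusted test for it; the paired Wilcoxon test compares a patient with himself and does not adjust the comparison of arms. Exploratory status excuses the lack of alpha control, but not a less precise estimate from a study meant to inform the next one. Planned extent, unlike baseline, may not be recoverable in usable form unless it is recorded beforehand.

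A reader might infer something stronger: that extent and baseline swamp any treatment effect, that they outweigh every plausible haemodynamic effect, or that hypothesis 2 cannot be answered. The documents do not support this. They give no SD, effect size or case mix; differences of about 0.9 SD remain detectable with the planned test; and chance imbalance in extent is ordinary sampling error, already covered by the p value and the confidence interval.

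**Conclusion.** The point holds as an avoidable loss of precision on a secondary, exploratory hypothesis. If baseline and extent explain 25–75% of the variance, the planned test detects about 0.91 SD at 80% power where an adjusted one would detect 0.77–0.44 SD. The SD passed to the follow-on trial is inflated by 1/√(1 − R²), a factor of 1.15 to 2.

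Three conditions apply. R² is assumed, not taken from the documents. The unadjusted test is unbiased only if allocation is random; the text at hand does not describe how patients are allocated, and under non-random allocation an imbalance in extent would be bias as well as noise. And the claim covers LiMAx and ICG clearance only. The capacity argument is most direct for LiMAx; for ICG clearance it rests on item 9 treating it as a liver-function measure taken before and after surgery. Nothing shows that liver Doppler or the laboratory values scale with the liver removed.

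**What to change.** Add to item 15, in substance: *Post-operative LiMAx and ICG clearance are compared between groups by rank-based ANCOVA, with the patient's own pre-operative value of the same test and the planned extent of resection (minor/major, recorded before surgery) as covariates. The unadjusted Mann-Whitney result is reported alongside.* A simpler alternative is a Mann-Whitney test on the ratio to baseline, stratified by planned extent. Report the adjusted residual SD next to the raw SD, so that the follow-on trial can be planned on either.

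Use the planned rather than the performed extent, because the course of the operation under the allocated management could alter what is finally done.

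The cost is one or two model terms in a small sample and one field on the case report form. No new test is needed if the pre-operative measurements are made as item 9 describes. The gain from extent is partial: a minor/major split captures only some of the extent-related variance, and less where the operation departs from the plan. The baseline term alone already brings part of the benefit.

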| b. Predicted future medical uses for patients (**Group benefit)** | It has to be the aim of this study to examine the influence of advanced haemodynamic monitoring and the use of clinical therapy protocols based on clinical studies to lower the rate of complications.  Given that this kind of surgery is common (approximately 250 interventions per year in the Department of General, Visceral and Transplantation sSurgery, Charité – University Medicine Berlin, Campus Virchow Clinic) and it is associated with a high rate of postoperative complications, the benefit of new knowledge is of high value for future patients to perform this intervention with a lower rate of complications. |

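### ICU stay, hospital stay and time to discharge criteria have no rule for death, and death is not an outcome; taken literally, an early in-hospital death ranks as a short stay

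*Protocol*

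**What the plan says.** Three durations appear among the secondary outcome measures in protocol item 4: ICU stay and hospital stay ("Length of intensive care stay and hospital stay (LOS") and "Time to fulfilling discharge criteria". Neither the outcome list nor the hypotheses name death or mortality.

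Item 15 states that "the primary and secondary endpoints will be analysed using non-parametric statistical tests", and for numerical outcomes it gives "quantitative data: Mann-Whitney-U test for independent groups or Wilcoxon-test for paired observations". It names no censoring, competing-event or worst-rank rule. It also says "The calculated p values will be considered as explorative and do not allow confirmative generalization", and it announces a later randomised trial whose sample size is to be calculated from these results.

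Item 14 fixes the size: "including 20 patients per group that means overall 60 patients are included".

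Follow-up is described in two ways. Items 23 and 27 end postoperative monitoring at discharge or day 8, whichever is earlier. Item 12 says discharge or 30 days.

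**The concern.** Each of these durations can end in two opposite ways. A hospital or ICU stay may be short because the patient recovered or because the patient died. A rank test on the recorded number of days cannot tell these apart, so an early death takes one of the best ranks. For time to discharge criteria the same patient never reaches the endpoint and has no value. One early death could therefore look favourable on two outcomes and be absent from the third, with no mortality outcome beside them to show it.

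Stay is not incidental here. Item 11a gives earlier discharge home as the expected benefit to the individual patient, and all eight studies in Appendix 1 report a reduction in hospital care. A stay effect distorted by deaths could be carried into the design of the follow-on trial. Item 11b says of the operation that "it is associated with a high rate of postoperative complications", which concerns complications rather than deaths but makes some deaths plausible.

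**Working it through.** **The plan's own figure.** The only one is the sample size: 3 groups x 20 = 60, as stated. There is no power calculation, and no death rate or stay distribution is given.

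**Setting.** I take a pairwise comparison of two arms with n = m = 20 and no ties. The protocol does not say whether the two goal-directed arms are ever pooled.

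**Effect of one death on the test.**
- U ranges from 0 to n x m = 20 x 20 = 400.
- Null SD of U = sqrt(n x m x (n + m + 1) / 12) = sqrt(400 x 41 / 12) = 36.97.
- If the stay of the patient who died is longer than k of the 20 stays in the other arm, moving that patient to the worst rank shifts U by 20 - k.
- k = 0 (shorter than every stay in the other arm): 20, which is 20/400 = 0.05 on the probability scale and 20/36.97 = 0.54 SD. This is the maximum.
- k = 10 (a median stay): 10/36.97 = 0.27 SD.
- k = 18 (a late death): 2/36.97 = 0.05 SD, close to nothing.
- Two or three deaths in one arm, all with k = 0: 40/36.97 = 1.08 SD and 60/36.97 = 1.62 SD.

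**How often a death would occur.** The rate p is an assumption. The chance of at least one death is 1 - (1 - p)^N.

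| Assumed p | Expected deaths in 60 | At least one in 60 | At least one in a given arm of 20 |
| --- | --- | --- | --- |
| 1% | 0.6 | 45% | 18% |
| 2% | 1.2 | 70% | 33% |
| 3% | 1.8 | 84% | 46% |
| 5% | 3.0 | 95% | 64% |

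If deaths fall at random, two deaths land in the same arm with probability 19/59 = 32%, and three with probability (19 x 18)/(59 x 58) = 10%.

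**Effect on error rates.** I used 4,000 simulated 20 v 20 comparisons with identical log-normal stays in both arms (assumed median 12 days, log-SD 0.5) and early deaths placed in one arm. The table gives the chance of a significant two-sided 5% result in favour of the arm with the deaths. The nominal value is 2.5%.

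| Early deaths in the arm | Scored as shortest stay | Excluded | Worst rank |
| --- | --- | --- | --- |
| 1 | 3.6% | 2.1% | 0.8% |
| 2 | 6.9% | 2.3% | 0.3% |
| 3 | 9.8% | 2.7% | 0.1% |

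A single early death has a modest effect. The distortion becomes material when two or three early deaths fall in the same arm.

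**The case against.** The strongest reply is that scoring deaths in length of stay is an analysis convention often left to an SAP, which is not at hand. The Mann-Whitney test accommodates worst-rank scoring as readily as raw days. A reader might infer that the plan deliberately counts death as a good result. The documents do not support that: they are silent, and short-stay scoring or drop-out is only what follows if the stated test is applied to the stated variable without further instruction. What survives is that item 15 is the protocol's own statistical section and already fixes the test, and that leaving death off the outcome list is a choice made in the protocol itself.

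A reader might also infer that deaths would go unseen or that safety monitoring is reversed. That does not follow. Item 27 provides study-physician visits and adverse event reports to the study director within 24 hours, item 13 allows the study to be stopped for untenable risk, and with 20 patients per arm deaths would be seen case by case. Nor does item 5 make mortality the main reason for the low-pressure strategy. It gives less bleeding as the goal and mentions mortality only in describing studies of the existing practice.

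Finally, the trial is a pilot with exploratory p values. The primary outcome, stroke volume before resection, cannot be altered by a postoperative death, and none of the three durations appears in a hypothesis. All of this stands and limits the weight of the point. It does not restore the direction of a comparison that early deaths have reversed, and descriptive medians of stay are affected in the same way.

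**Conclusion.** The point holds in a limited form. Applied literally, items 4 and 15 rank an early in-hospital death as a short ICU and hospital stay and leave it without a value for time to discharge criteria, and no death outcome offsets this. The shift is at most 0.54 null SD per death in a 20 v 20 comparison, less when the death is not among the shortest stays, near zero for a late death, and nil if nobody dies. How often this would arise rests on an assumed mortality of 1% to 5%, and the error rates rest on an assumed stay distribution. The consequence reaches only exploratory secondary outcomes and the planning of the next trial. The change is worth making because it costs little and is credible only if fixed before the data are seen.

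The conflict over follow-up bears on this. Under the day 8 version, recording of longer stays and later in-hospital deaths is not secured.

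**What to change.** - In items 4 and 15, state that a patient who dies in hospital receives the worst rank for ICU stay, hospital stay and time to discharge criteria. The planned Mann-Whitney test is otherwise unchanged.
- Show the plain durations in survivors beside the ranked result.
- Add in-hospital death, listed by arm, to the outcomes in item 4.
- Reconcile items 23 and 27 (discharge or day 8) with item 12 (discharge or 30 days), so that stay and in-hospital death are both recorded to discharge.

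The cost is a few sentences and no extra patients. If the day 8 version has governed data collection, recording must be extended to discharge for patients still in hospital. The small statistical drawback is that stay becomes a ranked composite of duration and death, which is why the survivors' durations should stand beside it. Days alive and out of hospital, or death treated as a competing event, would also be defensible; worst rank is suggested because it keeps the planned test.
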